##### Resource use will also be assessed

Resources to train SASH practitioners and resources involved in delivering SASH and TAU will be collected using two health economics inventory forms designed for the SASH trial.Health and social care service use and school support services use by young people will be assessed using the CSRI.^26^Productivity loss and family resource use due to the mental health difficulties of young people will be assessed using the CSRI.^26^

##### Practitioner-reported data

Demographic data.Participant attendance at follow-up sessions.

Outcome data will be collected from all participants. Retention in the trial will be maximised by conducting research assessments out of hours to accommodate young people and carer schedules and commitments. Measures will be completed flexibly via telephone, video conference, email or via text message if appropriate. Retention will also be enhanced by sending regular ‘staying in touch’ texts with study updates and thank you cards.

### Patient and public involvement

A YPAG was formed by the McPin Foundation. This consisted of 11 young people with lived experience of self-harm, suicidality and/or experience of ED care. The group was coordinated and chaired by two young adults with lived experience of mental health issues. In the development phase of the project, the team met with the YPAG every 3 months to advise on study design and to codevelop the SASH approach. For example, valuable feedback from the YPAG resulted in removing a previous exclusion criterion, excluding young people with autism from participating. Additional input included advice on progress, reviewing study materials and dissemination, co-creation of training videos and piloting measures. The YPAG plays a key role in advising on recruitment and retention, ethics and shaping operational procedures and dissemination. Members of the YPAG will be involved in the interpretation of all findings, in particular, the qualitative interviews.

### Independent committees

The trial has an independent project steering committee (PSC) and a data and ethics monitoring committee (DMEC). Both include a clinical academic, statistician, expert by lived experience and trialist. The DMEC ensures the safety, rights and well-being of participants by monitoring study progress, data and intervention completion rates, safety reporting and advising on ethical issues, making any relevant recommendations to the PSC.

### Data management

Personal information is stored at NHS Site or with the Sponsor, with hard copies stored in locked files, and electronic versions stored on encrypted servers, accessed by the study team only. Data will be entered by researchers into a secure bespoke RedCAP database stored on Sponsor servers and designed specifically for the trial with appropriate range checks for values. Adverse events are recorded in logs and their relatedness to the intervention is determined by site Principal Investigtors (PIs) who are all senior clinicians. Data monitoring is undertaken by the research team in collaboration with the Sponsor and recruiting sites.

### Analyses

#### Statistical analyses

The primary outcome is the number of episodes of self-harm in the last month measured 6 months after randomisation. This is a count outcome. Preliminary data^17^ suggest that the number of self-harm episodes is overdispersed in this population. A mixed-effects negative binomial regression model will estimate the effect of the intervention on the number of self-harm episodes, compared with TAU only. The model will adjust for number of self-harm episodes in the month prior to treatment and clustering of participants within crisis teams. The evidence for the effectiveness of the intervention will be assessed by a two-sided z-test of the log rate ratio, at *α*=0.05. Our primary analysis will be intention-to-treat. A per-protocol analysis will also be carried out. Sensitivity analyses will evaluate the robustness of conclusions to various statistical assumptions by fitting an additional random intercept for practitioners in the primary analysis model and by using different types of count model instead of negative binomial regression.

Exploratory analyses will be conducted on the fortnightly longitudinal measures of self-harm via text message survey. If sufficient data from the text message surveys are available, a longitudinal model for change in self-harm will be developed to investigate the trajectory of change and whether this varies between different subpopulations, especially minority ethnic, non-heterosexual and gender-diverse groups.

Secondary outcomes will be investigated using generalised linear mixed-effects models, accounting for clustering within crisis teams via random intercepts and using error distributions as appropriate depending on the measurement level and distribution of each secondary outcome.

Exact details of all analyses will be described in a statistical analysis plan, which will be finalised and signed off before the master database is locked on completion of data collection.

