### Trial design

See figure 1 for the trial design flowchart. The trial consists of a parallel group individually randomised trial with concealed allocation. Randomisation is conducted using permuted blocks and is stratified by CAMHS crisis team and whether the young person has presented to the ED more than one time (binary variable). Randomisation is conducted with 1:1 allocation through a secure internet-based system (REDCap). The randomisation sequence is generated by an independent, external statistician. Participants and clinicians are informed of allocation. The follow-up period is 6 months, with two follow-up assessments; the first is conducted postintervention (the intervention lasts around 8 weeks) or after the 7-day follow-up for young people allocated to TAU; the second and final assessment is conducted 6 months postrandomisation.

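### The primary model's stated adjustment set omits one of the two randomisation stratifiers, repeat ED presentation; adding it is a free improvement

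*Protocol article*

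**What the plan says.** Under Trial design, the article uses permuted blocks with 1:1 allocation, and randomisation "is stratified by CAMHS crisis team and whether the young person has presented to the ED more than one time (binary variable"). There are thus two stratification factors.

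Under Statistical analyses, the primary analysis is set out as follows: "A mixed-effects negative binomial regression model will estimate the effect of the intervention on the number of self-harm episodes, compared with TAU only". The next sentence gives the adjustment terms: "The model will adjust for number of self-harm episodes in the month prior to treatment and clustering of participants within crisis teams". Repeat ED presentation is not among them.

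The sensitivity analyses named there consist of "fitting an additional random intercept for practitioners in the primary analysis model and by using different types of count model instead of negative binomial regression". Neither brings the second stratifier in. The secondary-outcome models are described only in general terms, as "accounting for clustering within crisis teams via random intercepts". The section ends by leaving exact details to a SAP, which is not shown.

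**The concern.** A trial is best analysed with the factors it was randomised on. Stratified allocation balances the arms on repeat presentation, so the treatment estimate varies less from trial to trial than it would under simple randomisation. A model without the factor does not know this. It leaves the variation that the factor explains in the residual, and the model-based standard error describes a less balanced design than the one used. The two-sided z-test of the log rate ratio is then somewhat conservative.

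What is at stake is reported precision and power. The article has little power to spare: its 80% holds only if overdispersion is at most 0.28, and its own simulation check suggests that 0.15 or less may be needed.

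**Working it through.** **1. The plan's own figures.** 122 analysed and 15% attrition give 122 / (1 − 0.15) = 143.5, rounded up to 144, as stated.

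The 122 cannot be fully checked, because the assumed TAU rate is not given. In the Zhu–Lakkis formula with the variance taken under the alternative, n per group = (1.960 + 0.842)² × [(1/μ)(1 + 1/0.67) + 2k] / (ln 0.67)². With k = 0.28, n = 61 needs a TAU mean μ of about 3.6 episodes per month; the variants of the null variance bring this down to about 3.1. The present point does not depend on it, but a mean of 3.4 is used below to stay within that range.

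**2. The two lists side by side.**

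| Factor | Randomisation | Stated primary model |
|---|---|---|
| Crisis team | stratifier | clustering term |
| Repeat ED presentation | stratifier | not listed |
| Baseline self-harm count | not a stratifier | covariate |

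**3. Size by hand.** Let p be the share of repeat presenters and θ their outcome rate ratio (both assumed). The omitted log-scale variance is p(1 − p)(ln θ)². The per-participant variance averaged over arms is ½[1/3.4 + 1/(3.4 × 0.67)] + k = 0.367 + 0.28 = 0.647. The standard error without the term is larger by about √(1 + omitted variance / 0.647) − 1.

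- θ = 1.5, p = 0.5: 0.25 × 0.164 = 0.041; √(1 + 0.041/0.647) − 1 = 3.1%.
- θ = 2.0, p = 0.5: 0.25 × 0.480 = 0.120; √(1 + 0.120/0.647) − 1 = 8.9%.
- θ = 2.0, p = 0.3: 0.21 × 0.480 = 0.101; √(1 + 0.101/0.647) − 1 = 7.5%.

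Greater overdispersion shrinks the proportional loss. The cited pilot (mean 1.1, SD 1.6) implies k = (1.6² − 1.1)/1.1² = 1.2. With that k and the same mean of 3.4, the θ = 2.0, p = 0.5 case gives √(1 + 0.120/1.57) − 1 = 3.7%.

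**4. Simulation with the baseline count in the model.** Assumptions: permuted blocks of 4 within 6 teams × repeat presentation, n = 122, k = 0.28, and a negative binomial model with baseline count and fixed team effects (in place of the random intercept). There were about 1,500 runs per row. At the target rate ratio of 0.67:

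| θ | p | Power without | Power with | Mean SE without | Mean SE with | SE larger by |
|---|---|---|---|---|---|---|
| 1.0 | 0.5 | 77.7% | 78.1% | 0.146 | 0.145 | 0.7% |
| 1.5 | 0.5 | 76.3% | 78.2% | 0.149 | 0.146 | 2.1% |
| 2.0 | 0.5 | 76.1% | 80.3% | 0.156 | 0.145 | 7.6% |
| 2.0 | 0.3 | 71.7% | 76.3% | 0.156 | 0.146 | 6.8% |

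Under a null effect the corresponding SE increases are 0%, 2.9%, 8.8% and 8.0%.

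**5. Validity.** The mean estimated rate ratio was 0.67 in both models. Under the null, the rejection rate was 4.2–6.1% without the term and 4.6–7.3% with it. The Monte Carlo standard error is about √(0.05 × 0.95/1500) = 0.6 points, so the omission causes no inflation. The upper end with the term (7.3%, at θ = 2.0, p = 0.3) is above nominal. Part of the apparent power gain in that row therefore reflects a slightly liberal test.

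**6. Actual spread of the estimate.** At θ = 2.0, p = 0.5 and rate ratio 0.67, the empirical standard deviation was 0.152 without the term and 0.148 with it. Stratification has already delivered most of the balance; the stated model mainly fails to report it.

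**The case against.** The strongest reply is that this is a condensed article. Exact details go to a SAP signed off before database lock, the adjustment sentence does not say that its list is exhaustive, and nothing says the stratifier will be left out. That has weight, but the article is not silent on covariates. It states what the primary model adjusts for, and a SAP that follows it would repeat the omission.

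The reply is right on several further points, where a reader might infer more than the documents support:

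- **That the secondary-outcome models are wrong.** Their sentence says how clustering is handled. It is not a covariate list and does not mention baseline values either, so silence there is condensation and no error.
- **That the stratifier was chosen because it predicts self-harm.** The article gives no reason for the choice. Its background describes a cycle of repeat ED attendance, but does not offer this as the reason for stratifying.
- **That intervals will certainly be too wide.** This holds only if repeat presentation is prognostic given the baseline count, which is already in the model. At an assumed ratio of 1.0 there is essentially no cost.
- **That the trial's estimate becomes materially less precise.** Its actual spread barely changes; the loss is in the reported standard error and the power that follows from it.

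**Conclusion.** The mismatch between the randomisation factors and the stated primary adjustment set is plain in the text, and worth correcting. It does not threaten validity: a reader might infer bias or an inflated type I error, and neither appeared. The consequence is conditional and modest: roughly 0, 2 and 4 to 5 percentage points of power for assumed outcome rate ratios of 1.0, 1.5 and 2.0 among repeat presenters, at overdispersion 0.28 and 122 analysed. It would be proportionally smaller if overdispersion is greater.

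These figures rest on assumed prognostic ratios, shares of repeat presenters of 30–50%, a block size of 4 and team as a fixed effect; the documents give none of these. The point is best labelled a free improvement.

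**What to change.** In the SAP, before database lock, add the binary repeat-ED-presentation stratifier as a fixed covariate in the primary negative binomial model, next to the baseline count and crisis team. Carry it through the sensitivity analyses (practitioner intercept, alternative count models). For consistency, use the same term in the secondary-outcome models when their covariates are written out.

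The cost is one parameter. Stratified randomisation already requires the variable to be recorded for every participant, so no new data are needed, and neither the target of 144 nor any other stated figure changes.

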#### Sample size calculation

The measure of effect size is the rate ratio: the relative rate of the number of self-harm episodes post-treatment in the intervention group compared with the TAU group. A 33% reduction in self-harm episodes, relative to TAU, would constitute a clinically meaningful effect. This corresponds to a rate ratio of 0.67 and is at the ‘small effect’ end of the range of rate ratios observed in similar studies in adults.^1933^,^35^

Count outcomes used in trials are often overdispersed,^36^ and the amount of overdispersion (ie, the variance) has a large effect on statistical power.^37^ There is little published information about the variance of self-harm episodes per month in our target population. English *et al*^17^ present statistics on the number of self-harm episodes 6 months after TA based on n=14. They observed a mean of 1.1 with an SD of 1.6, indicating considerable overdispersion.

We performed a sensitivity check of our power analysis using a simulation approach with the simr package^40^ in R.^41^ We simulated data with the required properties, translating our estimates of within-participant correlation into a log rate ratio and within-practitioner correlation into a random intercept variance, and fitted an overdispersed Poisson regression model. Using 40 practitioners, total n=120 and 1000 simulated model runs, we found that overdispersion may need to be 0.15 or smaller for power to be reasonably certain to be at least 80% (estimated power: 83.7%; 95 % CI 81.3% to 85.9%).

#### Qualitative process evaluation

A qualitative process evaluation will be conducted using semistructured interviews with a purposively selected group of young people, parents/carers, trained practitioners and other staff in participating teams. Interviews will be audio recorded, transcribed and analysed using thematic analysis.^42 43^ Topic guides have been developed with support from the YPAG.

We will interview approximately 20 young people who received the SASH intervention to explore their experiences of the intervention, explore changes to managing self-harm and their well-being overall. Purposive sampling will be used to select young people with differential characteristics in terms of gender, ethnicity, whether or not they completed the intervention and whether the index ED visit was the first ED attendance or not. Interviews will be conducted soon after intervention completion to aid recall. Ten parents/carers will also be interviewed. These will be sampled based on whether or not they directly participated in the intervention. We will interview approximately 20 practitioners and other staff in participating teams, who will be purposively sampled according to their professional background and years of experience. We will also interview up to 20 young people and parents/carers in the TAU arm to explore their experiences of standard care. Purposive sampling will be used to select based on the demographic characteristics, such as sex, age, ethnicity and sexual orientation, and characteristics of the care received after ED presentation. Parents/carers will also be sampled based on their relationship with the young person.

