## Objectives

The objectives of the SASH study are as follows.

To assess whether the SASH intervention, in addition to standard care, reduces self-harm in young people who present to the ED with self-harm or suicidal ideation (with self-harm in the past month), compared with a TAU group who receive standard National Health Service (NHS) care only. To assess whether the SASH intervention improves secondary outcomes, including suicidal ideation, symptoms of depression and anxiety, school attendance, repeat ED attendance for self-harm or suicidal ideation, suicide and well-being.To explore how the intervention is experienced by participants, including minority ethnic, non-heterosexual and gender-diverse young people, and how it should be adapted appropriately for diversity among young people (eg, ethnicity, sexuality and gender).To assess the costs and cost-effectiveness of the intervention.

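### The SASH-arm interviews are not sampled on sexual orientation, although the third objective asks how non-heterosexual young people experience the intervention

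*Protocol article*

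**What the plan says.** The objectives in the protocol article are not numbered. The third in order is "To explore how the intervention is experienced by participants, including minority ethnic, non-heterosexual and gender-diverse young people", and it goes on to ask "how it should be adapted appropriately for diversity among young people (eg, ethnicity, sexuality and gender".

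The section on the qualitative process evaluation sets out two groups of interviews with young people.

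- **SASH arm.** "We will interview approximately 20 young people who received the SASH intervention to explore their experiences of the intervention". The purposive sampling rule reads: "select young people with differential characteristics in terms of gender, ethnicity, whether or not they completed the intervention and whether the index ED visit". Its last item separates first from repeat attendance.
- **TAU arm.** "We will also interview up to 20 young people and parents/carers in the TAU arm to explore their experiences of standard care". The sampling rule here is to "select based on the demographic characteristics, such as sex, age, ethnicity and sexual orientation, and characteristics of the care received after ED presentation".

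The section on statistical analyses mentions non-heterosexual young people once more. If the text-message surveys yield enough data, an exploratory longitudinal model will look at the course of self-harm and "whether this varies between different subpopulations, especially minority ethnic, non-heterosexual and gender-diverse groups".

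**The concern.** The objective names three groups and three matching axes of adaptation. The SASH-arm interviews are the part of the design that can report how the intervention was experienced, and their sampling characteristics match two of the three axes. The third, sexual orientation, appears only for interviewees who did not receive SASH and are asked about standard care.

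Applied as written, the SASH-arm criteria do nothing to secure interviews with non-heterosexual recipients. If few are interviewed by chance, the trial will have little to say on how they experienced the intervention or how it should be adapted for sexuality.

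**Working it through.** No figure in the article is at issue, so there is none to reproduce. The check is a comparison of texts, followed by an illustration of how large the risk could be.

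**Step 1: objective against sampling characteristics.**

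| Axis named in the third objective | SASH interviews (about 20; experience of the intervention) | TAU interviews (up to 20, including carers; experience of standard care) |
|---|---|---|
| Ethnicity | listed | listed |
| Gender | listed | sex listed |
| Sexuality | not listed | sexual orientation listed |

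The SASH list carries no wording that marks it as a set of examples. The TAU list is open, because its characteristics are introduced as examples.

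**Step 2: does anything else fill the gap?** The subgroup model under Statistical analyses concerns self-harm counts over time and depends on sufficient data; it does not measure experience of the intervention. Parents and carers are sampled on whether they took part directly in the intervention, and practitioners on professional background and years of experience. None of these secures the views of non-heterosexual SASH recipients.

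**Step 3: how much is left to chance?**

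Inputs:
- n = 20 SASH interviews (Qualitative process evaluation).
- p = share of non-heterosexual young people among SASH participants. The article gives none, so 10%, 20% and 30% are assumed.
- Selection is taken to be unrelated to orientation.
- Two or fewer is used as a marker of thin coverage. It is a working threshold, not one from the article.

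Formula: X ~ Binomial(20, p), so the expected number is 20p and P(X ≤ 2) = P(0) + P(1) + P(2), where P(k) = C(20, k) p^k (1 − p)^(20 − k).

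| Assumed p | Expected number | P(0) | P(1) | P(2) | P(X ≤ 2) |
|---|---|---|---|---|---|
| 10% | 2 | 0.122 | 0.270 | 0.285 | 0.677 |
| 20% | 4 | 0.012 | 0.058 | 0.137 | 0.206 |
| 30% | 6 | 0.001 | 0.007 | 0.028 | 0.035 |

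(Sums are taken before rounding.)

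**Step 4: finite pool.** The SASH arm has about 144 / 2 = 72 young people, so 20 interviews are a sizeable fraction of it. Drawing 20 of 72 without replacement (hypergeometric), with 7, 14 or 22 non-heterosexual participants among the 72 (about 10%, 19% and 31%), gives P(X ≤ 2) of 0.702, 0.180 and 0.016. The pattern is the same: high at the lowest share, small at the highest.

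**The case against.** **The list may be a summary.** A journal article condenses a full protocol, and a detailed sampling matrix may sit there. The objective sets no quota, and purposive sampling can be adjusted as interviews accrue. This has some force, and the full protocol could settle the matter. But the article does not leave sampling to another document. It states the characteristics for both arms, and those for the SASH arm do not match the stated objective.

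**The size rests on an assumption.** This stands. The result runs from 68% to 4% across the assumed shares, and the threshold is arbitrary. Having no non-heterosexual interviewee at all, which would defeat this part of the objective outright, has a probability of 12%, 1% and 0.1% at the three shares. At 30% or more the practical risk is small.

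**The timing may be too late.** This also stands in part. Randomisation was planned to end in April 2025, the intervention lasts around 8 weeks, interviews follow soon after completion, and the protocol version is dated 30 June 2025. If recruitment ran to plan, many SASH interviewees may already have been selected. Changing the criteria alone might then achieve little, so a reporting step is needed as well.

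**Stronger readings that the article does not support.** A reader might infer that sexual orientation was put on the wrong arm by mistake. Nothing shows this: the TAU interviews have their own purpose, for which orientation is a legitimate characteristic. A reader might also infer that non-heterosexual young people are left out of the SASH interviews or that the objective cannot be met. The criteria exclude nobody, and at the higher assumed shares chance alone would probably bring in several.

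**Conclusion.** The concern holds as a mismatch between a stated objective and a stated sampling rule. The SASH-arm interviews are sampled on two of the objective's three axes, and nothing else in the article secures non-heterosexual young people's account of the intervention.

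The consequence is a possible shortfall, not a certain one. It is material if the share of non-heterosexual participants is about 20% or lower, and minor at about 30% or higher. That judgement rests on the assumed shares, on selection unrelated to orientation, and on reading the SASH list as complete. The primary analysis and the sample size are not touched.

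**What to change.** In the section on the qualitative process evaluation, add sexual orientation to the purposive sampling characteristics for the SASH-arm interviews still to be selected. Keep the number at about 20.

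Where interviews are already complete, report how many SASH interviewees were non-heterosexual, and limit conclusions on experience and adaptation by sexuality to what that number can bear.

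The cost is one phrase in the protocol and one more dimension to balance across 20 interviews. No extra interviews are required. The characteristic appears to be available already, since the TAU sampling and the exploratory subgroup model both rely on it, although the article does not list it as a data item by name.
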